## Exclusion criteria

1. Patients allready diagnosed with dementia.
2. Patient or (if present) caregiver terminally ill.
3. Permanent admission of the patient to a nursing home expected within 6 months.
4. The patient is not/no longer sufficiently capable of understanding spoken language or expressing him- or herself.

Diagnostic Test Accuracy Study: In order to also get information about the negative predictive value of the FPs cognitive classification, an additonal sample will be drawn of patients FPs classified as ‘no signs of cognitive impairment’ (Figure 2).

The study population for the process evaluation of succes and failure factors of the intervention consists of FPs and practice nurses in the intervention group. In addition, a random selection of patients and caregivers in the intervention group is invited to participate in a semi-structured interview.

## Sample size calculation

In order to come to a sample size that would allow showing significant differences in quality of care, in wellbeing and in numbers of new dementia diagnoses we performed several power calculations:

Quality of care:

The primary outcome is the difference in total score on a set of quality indicators (QIs) after 12 months between intervention and control group. Perry et al. found a mean (crosssectional) concordance to the total set of 45.3% (SD 30.4). A serial measurement is not yet done with this set of QIs.

For this study we expect an increase in concordance in the intervention group of around 1.5 times the baseline scores. In other words; an added 22,5% concordance with the total set of QIs is considered as clinically relevant. We based out powercalculation on the method described by Kerry et al.(Kerry and Bland 1998). To be safe we assumed a somewhat larger within cluster SD of 35 than Perry et al. found. Based on research of Campbell et al on ICCs in primary care research we assumed a between cluster SD of 3(Campbell et al. 2005).

With an α of 0.05 and β of 0.90, a sample size of 5 clusters per arm and 72 patients per arm is required to show a statistically significant and clinically relevant difference in quality of care.

Caregiver wellbeing:

We chose the GHQ12 as a meausure of caregiver mental health as the most important patient and caregiver wellbeing measure. We expect to find results after a period of 12 months on this outcome. We based our sample size for the GHQ 12 on a study of Diaz et al . in 2008. They report a significant difference in GHQ 12 decline between intervention and control group. The average difference in decline was 2.2 points in a period of 6 months. Based on their SDs we (conservatively) estimated SDs in the control- (4.3) and interventiongroup (3.6). Based on the formula: √(SDbaseline2 x SDfollow-up2).

A paired t-test for average difference with unequal variance shows that assuming an equal distribution over intervention and controlgroup,a desired power of 90%, and an alpha of 0.05 we need to include 57 caregivers per group in order to find significant and clinically relelvant results (SASsoftware). Estimating that about half of patients will have an informal caregiver and that about 20% will be lost to follow-up in the first year and adding 10 % for clustering resulted in a desired sample of 156 patients per arm.

Number of new dementia diagnoses in 12 months:

We based this calculation on a previous study on an educational intervention to improve the number of dementia diagnoses in primary care(Perry et al. ). Perry et al. conducted a cluster RCT design in which they asked 105 FPs to select 5 patients in whom they suspected cognitive impairment. FPs collaborated with a practice nurse in diagnosing dementia. In the intervention group, dementia was diagnosed in 49.1% (130 new diagnoses in 265 patients at risk) of these patients, in the control group in 14.8% (20 new diagnoses in 135 patients at risk) of these patients, after one year. Using the probabilities of Perry et al. and assuming a power of 90%, 20% loss to follow-up and adding 10% for clustering within practices resulted in a desired sample of 55 patients per arm.

Diagnostic accuracy of FPs’ classification at baseline

The diagnostyic accuracy is expressed in the positive and negative predictive value of the FPs at baseline. When we include 312 patients, initially classified by the FPs as cognitive impaired as well as and100 patients initially classified with no cognitive impairment, we reach a confidence interval of 17.9% around the point estimate, assuming a prior positive predictive value of 30%.

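### On the stated GHQ-12 inputs, 57 caregivers per group gives 90% power only with a one-sided 0.05 test, which the protocol nowhere states; at two-sided 0.05 the power is about 83.5%

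*Protocol*

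**What the plan says.** Everything here is in the protocol, section 4.4 (Sample size calculation), under caregiver wellbeing.

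- **Effect:** taken from a cited study: "The average difference in decline was 2.2 points in a period of 6 months".
- **Spread:** the authors "estimated SDs in the control- (4.3) and interventiongroup (3.6"), with the derivation given as "Based on the formula: √(SDbaseline2 x SDfollow-up2").
- **Test:** "A paired t-test for average difference with unequal variance", "assuming an equal distribution over intervention and controlgroup".
- **Result:** "a desired power of 90%, and an alpha of 0.05 we need to include 57 caregivers per group".
- **Inflation:** about half of patients have a caregiver, 20% are lost in the first year, and "adding 10 % for clustering resulted in a desired sample of 156 patients per arm".

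The same section asks for 72 patients per arm for quality of care and 55 per arm for new dementia diagnoses. The GHQ-12 figure is the largest, and twice 156 is the 312 patients given in the Summary. The protocol does not say whether alpha is one- or two-sided.

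**The concern.** An alpha of 0.05 with no qualifier is conventionally read as two-sided. On that reading the stated inputs call for clearly more than 57 caregivers per group, so the claim of 90% power does not follow from them. This is the calculation that sets the size of the trial, and the protocol treats GHQ-12 as its leading wellbeing measure. A reader would take the chance of missing a true 2.2-point difference to be 10%, when on the stated assumptions it is about 16.5%.

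Two statements in the same paragraph make the figure hard to audit. The test is called paired although it compares change between two separate arms. The SD formula is printed as a product, which does not yield a standard deviation of change.

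**Working it through.** **Inputs (section 4.4):** difference 2.2; SDs 4.3 (control) and 3.6 (intervention); equal groups; power 90%; alpha 0.05, sidedness unstated.

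**1. Reproducing 57.** The root-mean-square SD is √((4.3² + 3.6²)/2) = √15.725 = 3.965.

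Normal approximation, n per group = 2 × 15.725 × (z_alpha + z_power)² / 2.2²:
- One-sided: 31.45 × (1.645 + 1.282)² / 4.84 = 55.6, so 56.
- Two-sided: 31.45 × (1.960 + 1.282)² / 4.84 = 68.3, so 69.

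Noncentral t with Welch degrees of freedom. At n = 57 the noncentrality is 2.2 / √(31.45/57) = 2.96 on about 109 df.

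| n per group | one-sided 0.05 | two-sided 0.05 |
|---|---|---|
| 56 | 89.8% | 82.9% |
| 57 | 90.3% | 83.5% |
| 69 | 94.5% | 89.9% |
| 70 | 94.7% | 90.3% |

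So 57 is exactly the smallest one-sided sample size, and 70 is the two-sided one. The normal approximation puts the two-sided power of 57 at 84.2%.

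One other route also gives 57: a two-sided normal approximation with SD 3.6 in both arms, 2 × 3.6² × (1.960 + 1.282)² / 4.84 = 56.3. It discards the stated 4.3 and the unequal-variance test, so it does not rescue the claim either.

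**2. Effect on the trial size.** The protocol's chain is divide by 0.5, divide by 0.8, multiply by 1.1.
- 57: 57 / 0.5 / 0.8 × 1.1 = 156.75, stated as 156.
- 70: 70 / 0.5 / 0.8 × 1.1 = 192.5, so 193 per arm and 386 in total.

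Working back, 156 × 0.5 × 0.8 / 1.1 = 56.7 effective caregivers per arm, with two-sided power 83.4%.

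**3. Which sidedness does the rest of section 4.4 use?** The diagnoses calculation takes 49.1% against 14.8%, 90% power, 20% loss and 10% for clustering, and arrives at 55 per arm. With Δ = 0.343 and the unpooled variance 0.491 × 0.509 + 0.148 × 0.852 = 0.376:
- Two-sided: n = (1.960 + 1.282)² × 0.376 / 0.343² = 33.6. The continuity correction (n/4)(1 + √(1 + 4/(nΔ)))² gives 39.2, so 40, and 40 / 0.8 × 1.1 = 55.
- One-sided, same method: 27.4, corrected 32.9, so 33, and 33 / 0.8 × 1.1 = 45.4.

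Other two-sided variants (pooled variance, with or without the correction, multiplying by 1.2 instead of dividing by 0.8) run from about 49 to 60. One-sided variants reach at most about 50. The stated 55 therefore fits a two-sided alpha better. The quality-of-care figure of 72 exceeds both its two-sided (about 55) and one-sided (about 44) recalculation, so it does not discriminate.

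**4. The SD formula.** √(SDb² × SDf²) equals SDb × SDf, which is in squared points. A change SD is √(SDb² + SDf² − 2r·SDb·SDf). If the multiplication sign is a slip for a plus, 4.3 and 3.6 are the r = 0 case. With equal baseline and follow-up SDs, a positive r then shrinks both by √(1 − r). Two-sided power at 57 would be 90.0% at r = 0.18 and 98.6% at r = 0.5 (r is assumed; the protocol gives none). If the product is taken literally with equal SDs, the r = 0 change SDs are √(2 × 4.3) = 2.93 and √(2 × 3.6) = 2.68, and the power is about 98.5%.

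**5. The caregiver share.** Section 4.4 assumes half of patients have a caregiver. Inclusion criterion 2 (section 4.2) requires an identifiable primary caregiver, and Figure 2 shows patient and caregiver outcomes for 156 per arm. Exclusion criterion 2 (section 4.3), by contrast, allows for a caregiver being absent. If every patient has one, 156 × 0.8 / 1.1 = 113 effective caregivers per arm, with two-sided power 98.6%.

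**The case against.** The best defence is that sidedness is unstated, not contradicted: if a one-sided 0.05 test was intended, 57 and 90% are arithmetically right. That is true, but it moves the defect without removing it. No section announces or justifies a one-sided test, section 9.3 speaks only of comparing the two conditions, and the diagnoses figure points the other way.

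Three stronger readings are tempting, and the document does not support them.

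- **That the diagnoses figure proves a two-sided alpha.** It does not. One two-sided route lands on 55 and others bracket it, but the method is not stated, so this is an inference from a separate calculation.
- **That the trial will deliver only 83% power for GHQ-12.** That depends on the half-with-caregiver assumption, which conflicts with inclusion criterion 2, and on SDs whose printed derivation is faulty. Either could raise the figure well above 90%. The baseline-adjusted model in section 9.3 may also recover some power.
- **That the primary outcome is underpowered.** Quality of care is primary, and by the protocol's own figure it needs 72 per arm against 156 planned.

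The objection that the paired label and the product are mere wording stands in part. The mention of unequal variance and the per-group count already show that two groups are meant. The formula still matters, because it is the only stated source of the SDs that drive the result.

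**Conclusion.** The point holds as a misstatement of power on the protocol's own inputs. With a difference of 2.2, SDs of 4.3 and 3.6 and equal groups, 57 per group has 83.5% power at two-sided 0.05 (84.2% by the normal approximation), against 90% claimed. Reaching 90% takes 70 per group, or about 193 patients per arm by the same inflation. The claim is met only at one-sided 0.05, which is undisclosed.

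The conclusion rests on reading an unqualified alpha of 0.05 as two-sided and on taking the SDs as given. Translating it to 156 patients per arm also requires that half of patients have a caregiver. It should be fixed, but the outcome is secondary and nothing here shows that more patients are needed.

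**What to change.** In section 4.4:

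1. Keep 156 patients per arm and state that alpha is two-sided.
2. Restate the GHQ-12 power as about 83-84%, conditional on SDs of 4.3 and 3.6 and on half of patients having a caregiver.
3. Name the test as a two-sample unequal-variance (Welch) t-test on change from baseline, not a paired test.
4. Replace the product with √(SDb² + SDf² − 2r·SDb·SDf), giving the source SDs and r. If this changes 4.3 or 3.6, recompute the power from the corrected values; these then replace the 83-84%.
5. Reconcile the half-with-caregiver assumption with inclusion criterion 2 and Figure 2, and give the power for whichever applies (about 98-99% if every patient has a caregiver and the SDs stand).

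The cost is protocol wording and a short recalculation. No patients are added and no analysis changes. On the stated assumptions the quoted power becomes less favourable.

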**Study design:**

Ad 1-3) Cluster Randomised Controlled Trial.

Intervention: collaborative diagnostic evaluation and management.

A trained practice nurse invites patients with suspected cognitive impairment for a comprehensive geriatric assessment, including a cognitive screening. If this assessment suggests the presence of MCI or dementia, it is followed by a more thorough assessment, including physical and neurological examination and laboratory tests, by the FP. When this results in a MCI or dementia diagnosis, the practice nurse in close collaboration with the FP will offer patients collaborative care. This consists of psycho education and support. In addition the practice nurse according to their needs as identified will coordinate care after a geriatric assessment.

Controls: Care as usual will be offered by the FP.

Ad 4) Diagnostic Test Accuracy Study: cross-sectional comparison of FPs’ recollections of the presence or absence of cognitive impairment in their patients ≥ 65 years, with reference standard diagnoses on the presence or absence of MCI or dementia.

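### The GHQ-12 calculation that sets the trial at 156 patients per arm makes no allowance for the share of suspected patients who are diagnosed, so its 90% power is not supported

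*Protocol*

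**What the plan says.** **Sizing.** Section 4.4 (Caregiver wellbeing) singles out the caregiver GHQ-12 as the leading wellbeing measure. The effect comes from an earlier study: "The average difference in decline was 2.2 points in a period of 6 months". The estimated SDs are 4.3 (control) and 3.6 (intervention). The calculation is made "assuming an equal distribution over intervention and controlgroup,a desired power of 90%, and an alpha of 0.05", without saying whether the test is one- or two-sided, and concludes that "we need to include 57 caregivers per group in order to find significant and clinically relelvant results". It then reaches 156 patients per arm: "Estimating that about half of patients will have an informal caregiver", 20% lost in the first year, and 10% added for clustering. The other two between-arm calculations need 72 (quality of care) and 55 (diagnoses) per arm, so this one fixes the total of 312.

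**Who is sampled.** Inclusion criterion 1 admits patients whom the family physician (FP) merely suspects of impairment. Criterion 2 requires an identifiable primary informal caregiver.

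**Who receives the care.** The Summary says: "When this results in a MCI or dementia diagnosis, the practice nurse in close collaboration with the FP will offer patients collaborative care". Section 5.1 reads more broadly. It aims the intervention at the whole suspected group and has the extra nurse assess needs and prepare care plans there, involving the caregiver.

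**How many are expected to be diagnosed.** Section 4.4 sizes the accuracy study "assuming a prior positive predictive value of 30" per cent. For an earlier trial's intervention arm it reports that "dementia was diagnosed in 49.1% (130 new diagnoses in 265 patients at risk) of these patients". Figure 2 expects about 50 of 156 per arm with dementia.

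**Who is analysed.** Research question 3 concerns diagnosed patients and their relatives. Figure 2 lists follow-up outcomes in patients with a baseline CAMCOG diagnosis of MCI or dementia, yet still gives about 156 for each arm.

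**The concern.** The 2.2-point difference is applied to 57 caregivers drawn from all suspected patients in an arm. If the care that should help caregivers follows only after a diagnosis, and well under all suspected patients are diagnosed, one of two things happens. Either the whole-arm difference is smaller than 2.2 points, or, if only diagnosed patients are analysed, there are far fewer than 57 caregivers per arm. Section 4.4 allows for neither.

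This matters because the calculation sets the trial's size and carries a 90% power claim for its leading wellbeing measure. A null GHQ-12 result read against 90% power would look like good evidence that caregivers do not benefit. With the power actually available, it may not be.

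**Working it through.** **1. Reproducing the plan's figures.** Two independent groups, unequal SDs: n = (z_α + z_β)² × (4.3² + 3.6²) / 2.2², with 4.3² + 3.6² = 18.49 + 12.96 = 31.45.

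- Two-sided 0.05, 90%: (1.960 + 1.282)² × 31.45 / 4.84 gives 69 (70 with the Welch t).
- One-sided 0.05, 90%: (1.645 + 1.282)² × 31.45 / 4.84 gives 56 (57 with the Welch t).

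So 57 is reproduced one-sided only. With 57 per group, SE = √(31.45/57) = 0.743, and Welch power at 2.2 points is 90% one-sided or 84% two-sided.

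Scaling: 57 / 0.5 / 0.8 × 1.1 = 156.75, which matches 156. No factor covers the diagnosed share.

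**2. Whole arm, 57 caregivers per group.** Assumption: full effect if diagnosed, none otherwise. Expected difference = 2.2 × share. The 60% and 80% rows are assumed shares, to cover MCI diagnoses that the 49.1% leaves out.

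| Diagnosed share | Difference | Power, two-sided | Power, one-sided |
|---|---|---|---|
| 30% | 0.66 | 14% | 22% |
| 49.1% | 1.08 | 30% | 42% |
| 60% (assumed) | 1.32 | 42% | 55% |
| 80% (assumed) | 1.76 | 65% | 76% |
| 100% (as in the plan) | 2.20 | 84% | 90% |

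**3. Whole arm, half the effect in the undiagnosed (assumed).** At 30%: 2.2 × (0.30 + 0.5 × 0.70) = 1.43 points, 48% two-sided (61% one-sided). At 49.1%: 2.2 × (0.491 + 0.5 × 0.509) = 1.64 points, 59% two-sided (71% one-sided).

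**4. Diagnosed patients only, full 2.2 points.** Caregivers per arm: 57 × 0.30 = 17.1 to 57 × 0.491 = 28.0. Power is 35 to 53% two-sided, 48 to 66% one-sided.

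**5. A caregiver for every patient (inclusion criterion 2).** Effective caregivers per group: 156 × 0.8 / 1.1 = 113.

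- Whole arm, no effect in the undiagnosed: 24% (share 30%) to 53% (share 49.1%) two-sided; 35 to 65% one-sided. Two-sided power reaches 90% only at a share of about 80% (91% there).
- Diagnosed only: 113 × 0.30 = 33.9 and 113 × 0.491 = 55.5 caregivers, giving about 60 to 83% two-sided and 72 to nearly 90% one-sided.

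**The case against.** Several objections have force.

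- **The diagnosed share is uncertain.** The 49.1% counts dementia only, so it is not a ceiling for MCI or dementia. The 30% is a prior predictive value used for a confidence-interval width, and Section 4.4 does not say whether it includes MCI, although the accuracy study's reference diagnosis does. Figure 2 expects about 32% (50/156) with dementia alone. These are also shares of patients, and caregivers may be concentrated among the more impaired. All of this stands, and it is why higher shares are shown.
- **Zero effect in the undiagnosed is contestable.** Section 5.1 describes needs assessment and care plans for the whole suspected group. That conflicts with the Summary, and the document does not settle it. Appendix 1 does not help, because its flow lines are not legible in the available text. Step 3 shows that even half the effect does not restore 90% at 30 to 49.1%.
- **Dilution may not be the mechanism.** Research question 3 and Figure 2 point to an analysis in diagnosed patients, where the shortfall is in numbers. This also stands. The omission then reappears as Figure 2's count of about 156 for a subset.
- **Inclusion criterion 2 contradicts the assumption that half have a caregiver.** Applying it roughly doubles the caregivers and raises power considerably.

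A reader might infer that true power is simply 14 to 30% instead of 90%. The documents do not support that. It sets two-sided results against a figure obtained only one-sided, and takes one corner of a wide range. Nor do they support the inference that a null result is the likely outcome, or that the trial as a whole is underpowered.

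**Conclusion.** The calculation that fixes the trial at 156 per arm omits the diagnosed share, while other parts of the protocol tie both the care and the wellbeing outcomes to a diagnosis. With Section 4.4's own caregiver assumption and 30 to 49.1% diagnosed, the claimed 90% is not delivered whether the whole arm or only the diagnosed patients are analysed. The like-for-like falls in the whole arm are from 84% to 14–30% (two-sided) or from 90% to 22–42% (one-sided), if the undiagnosed gain nothing.

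The exact power cannot be fixed from the document, because it depends on the analysis population, the diagnosed share, any effect in the undiagnosed, the caregiver share and the sidedness. Under favourable combinations, such as a caregiver for every patient and about 80% diagnosed, 90% two-sided is attainable.

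This should be fixed, but it does not threaten the trial's main comparison. GHQ-12 is secondary, and the primary quality-of-care calculation (72 per arm) does not depend on it.

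**What to change.** In Section 4.4:

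- name the GHQ-12 analysis population and state whether the test is one- or two-sided;
- enter an explicit diagnosed share (saying whether MCI counts) and an explicit caregiver share;
- replace the 90% claim by the resulting power range under stated assumptions;
- say that a null GHQ-12 result will be described as inconclusive.

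Reconcile the passages that disagree: research question 3, the Summary's study design, inclusion criterion 2, Section 4.4, the intervention description in Section 5.1, and the counts of about 156 in Figure 2.

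Baseline CAMCOG status is the natural way to define a diagnosed subset, but it cannot be adopted yet. A footnote in Appendix 3 limits the CAMCOG to the intervention arm, whereas Figure 2 shows it in both. That must be settled first. CAMCOG status is also not the FP's diagnosis that triggers care, so some dilution could remain in that subset. Diagnoses made during the trial would be a poor substitute, since Section 4.4 itself expects their frequency to differ by arm (49.1% against 14.8% in the earlier trial).

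The cost is rewording and a less favourable stated power. No extra patients or visits are needed.

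### The 17.9% confidence interval planned for the diagnostic accuracy study does not follow from a PPV of 30% in 312 patients, where the 95% full width is about 10.2 points

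*Protocol*

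**What the plan says.** Protocol section 4.4 (Sample size calculation), under diagnostic accuracy, names two measures: "The diagnostyic accuracy is expressed in the positive and negative predictive value of the FPs at baseline". It then gives the numbers, beginning "When we include 312 patients, initially classified by the FPs as cognitive impaired" and adding 100 patients classified as having no impairment. One precision figure follows for the two samples together: "we reach a confidence interval of 17.9% around the point estimate, assuming a prior positive predictive value of 30" (per cent).

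Section 4.3 says what the second sample is for: "In order to also get information about the negative predictive value of the FPs cognitive classification, an additonal sample will be drawn" from patients whom the FPs saw as showing no signs of impairment. The Summary, section 3 and Figure 2 give the same sizes, 312 and 100.

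For this calculation the protocol states no confidence level, no assumed NPV and no clustering allowance, and does not say whether 17.9% is a full width or a half-width.

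**The concern.** A predictive value is a proportion within one side of the classification. The PPV has the 312 FP-positive patients as its denominator and the NPV has the 100 FP-negative patients. A single interval tied to a PPV of 30% should therefore follow from 312, and 17.9% is much too wide for a sample of that size.

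This sentence is the only planning statement for research question 4 and secondary objective b. If it is wrong, the protocol does not tell the reader what precision the PPV will have. It also gives no reasoned precision for the NPV, although the 100 patients are recruited specifically to estimate it.

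**Working it through.** **Inputs.** From section 4.4: n = 312 (FP-positive), n = 100 (FP-negative), PPV 30%, stated interval 17.9%. From the Summary and Figure 2: 16 practices, hence 312/16 = 19.5 patients per practice. The 95% level is an assumption. It matches the quality-of-care calculation in the same section ("With an α of 0.05 and β of 0.90") but is not stated here.

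**Formula.** Full Wald width = 2 × 1.96 × √(p(1−p)/n).

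**Trying to reproduce 17.9% at p = 0.30**
- n = 312: 2 × 1.96 × √(0.21/312) = 2 × 1.96 × 0.02594 = 0.1017, that is 10.2 points, or ±5.1.
- n = 100: 2 × 1.96 × √(0.21/100) = 2 × 1.96 × 0.04583 = 0.1796, that is 17.96 points, or ±9.0.
- Solving for a full width of 0.179: n = 4 × 1.96² × 0.21/0.179² ≈ 100.7.

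The stated figure is 17.9/10.17 ≈ 1.8 times the width that belongs to the PPV.

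**Other readings of the PPV figure**

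| Reading (p = 0.30) | Full width, points |
|---|---|
| n = 312, Wilson 95% | 10.1 |
| n = 312, Clopper-Pearson 95% | 10.5 |
| n = 312, Wald 90% | 8.5 |
| n = 312, Wald 99% | 13.4 |
| 20% fewer patients (n = 250), Wald 95% | 11.4 |
| One arm only (n = 156), Wald 95% | 14.4 |
| All 412 patients, Wald 95% | 8.9 |

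None gives 17.9. Read as a half-width, 17.9% would correspond to about 25 patients, which is neither sample.

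**Clustering.** To reach 17.9 with n = 312, the design effect would have to be (17.9/10.17)² ≈ 3.1. At 19.5 patients per practice that means an ICC of (3.1 − 1)/18.5 ≈ 0.11. With assumed ICCs, the PPV width is 10.17 × √(1 + 18.5 × ICC):
- ICC 0.01: 10.17 × √1.185 ≈ 11.1
- ICC 0.05: 10.17 × √1.925 ≈ 14.1
- ICC 0.10: 10.17 × √2.85 ≈ 17.2

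**NPV, illustration only** (n = 100; the protocol assumes no value)
- NPV 90%: Wald width 11.8 (±5.9), Wilson 11.9, Clopper-Pearson 12.7.
- NPV 95%: Wald width 8.5 (±4.3), Wilson 9.0, Clopper-Pearson 9.6.

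**The case against.** **The origin of 17.9 is not documented.** A reader might infer that the authors put the PPV assumption into the NPV sample. The match is close, but 17.96 rounds to 18.0, so 17.9 needs truncation. The same width results from an NPV of 30% or 70% in 100 patients, and 17.9 also results from 312 patients with a design effect of about 3.1. The protocol states none of these routes. This part of the objection stands: n = 100 is consistent with the figure but not shown to be its source.

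**Clustering is plausible.** The patients come from 16 practices and the test is the FPs' own impression, so 10.2 points is the width before clustering, not the precision that will be achieved. That also stands. It does not rescue the sentence, because no ICC or design effect is given for this calculation. The 10% addition in section 4.4 belongs to the GHQ-12 and new-diagnosis calculations. At 19.5 patients per practice it would mean an ICC of only about 0.10/18.5 ≈ 0.005, and it should not be carried over without justification.

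**The consequence is small.** 17.9 is wider than the unclustered PPV interval and wider than the illustrative NPV intervals. The 156 patients per arm come from the GHQ-12 calculation, and the accuracy sentence only reports what precision those numbers deliver. Accuracy is a secondary objective. All of this stands, and it limits the weight of the point without making the figure right.

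**Conclusion.** The stated 17.9% is wrong for the estimate it names. With a PPV of 30% in 312 patients, the 95% full width is about 10.2 points (±5.1). This rests on a 95% level, which section 4.4 does not state for this calculation, and on independent patients. Changing the level to 90% or 99%, or changing the interval method, does not bring the figure to 17.9.

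The error understates the PPV precision. A reader might conclude that the accuracy study is too small, or that the 100 FP-negative patients were sized on the wrong proportion. The documents support neither. The misstatement hides no shortfall, and nothing shows that the 100 was derived from any assumed proportion. What can be said is that no NPV is assumed, so the protocol gives no basis for the precision of that estimate. The primary outcome and all sample sizes are unaffected. It is a reporting error worth correcting because it is the only precision figure for research question 4.

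**What to change.** Replace the sentence in section 4.4 with a separate statement for each estimate, giving n, confidence level and whether the figure is a half-width or a full width.

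- **PPV:** 30% in 312 patients gives ±5.1 points at 95% before clustering.
- **NPV:** give the precision in 100 patients at a value that the authors assume and justify. The ±5.9 (at 90%) and ±4.3 (at 95%) above are illustrations, not proposed text. Near 95% a Wilson or exact interval is preferable to Wald. Figure 2 stratifies this sample by age, gender and GP to mirror the first, so the authors should also say whether the simple-random-sample formula is meant as an approximation.
- **Clustering:** if an allowance is made, state it with its ICC. Assumed ICCs of 0.01 to 0.10 give PPV widths of about 11 to 17 points, so the choice matters. Do not borrow the 10% used for other outcomes.

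The cost is one rewritten sentence. No sample size, procedure or analysis changes.
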